## Discussion

As cancer incidence rises, cost-effective models of care that improve quality/equity of care for patients/carers are increasingly critical. Despite treatment breakthroughs, 29 advanced cancer-related deaths occur daily in Victoria, Australia, and 8.2 million deaths annually worldwide (http://www.cancerresearchuk.org/health-professional/cancer-statistics/worldwide-cancer/mortality). Those with advanced disease report high needs and distress that are inadequately addressed. Meanwhile, palliative care which explicitly addresses these concerns [11–17], is accessed variably and late [15, 34, 38]. STEP Care addresses the barriers to engagement with palliative care through routine time of introduction thereby reducing variability and standardisation of delivery of care.

The establishment of feasibility and the qualitative data from this study will inform the conduct of a subsequent study. Meanwhile, the key secondary outcome of quality of life and the effect size will enable robust calculation of the sample size of a phase 3 trial of STEP Care versus usual care alone. Therefore, outcomes of this phase 2 study, if successful, will provide strong support for a full phase 3 trial using defined transition points, measuring quality of life outcomes and will facilitate parallel implementation research. This study will address the as yet unresolved issue about the appropriate timing of early palliative care.

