We present the protocol of our trial that will test the feasibility of a novel standardised outpatient model of early palliative care [Standardised Early Palliative Care (STEP Care)] for advanced cancer patients and their family carers, with referrals occurring at the defined disease-specific evidence-based transition points. Testing integration of palliative care based upon transition points makes this a world-first study, with resulting data used to refine the model and data collection processes, identify issues with participant consent/retention, calculate effect sizes to inform a phase 3 trial to establish patient/carer benefits and cost implications and evaluate the timing of palliative care introduction according to patient and family carers.

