## Methods

### Primary aim

To determine the feasibility of conducting a definitive phase 3 randomised trial, which evaluates effectiveness of STEP Care (compared to usual best practice cancer care) for patients with advanced breast or prostate cancer or HGG. The specific feasibility endpoint is defined as enrolment of 90 patients across three sites in 24 months, with at least 60% of patients progressing to study completion, defined as 12 weeks post baseline. This will inform the planning of a subsequent phase 3 study including numbers of centres necessary to recruit the required sample size.

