### Secondary aims

To examine preliminary efficacy of STEP Care on patient outcomes, including quality of life, mood, symptoms, illness understanding and overall survival.To examine preliminary efficacy of STEP Care on caregiver outcomes, including quality of life, mood, preparedness to care and satisfaction with care.To document the impact of STEP Care on health service use in the last month of life based on parameters of established quality end-of-life indicators, including hospital and intensive care length of stay, emergency department admissions, chemotherapy use and place of death.To evaluate the timing of palliative care introduction according to patients, families and health care professionals.

The key secondary outcome of effect upon quality of life will enable the appropriate sample size calculation for a robust phase 3 trial.

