### Design

This study will involve a phase 2, multicenter, open-label, parallel-arm, randomised controlled trial (RCT) of STEP Care plus standard best practice cancer care versus standard best practice cancer care alone. This RCT has been designed within the Medical Research Council (MRC) framework for the development and testing of complex interventions [28, 31]. The MRC framework prioritises phased, sequential and intervention development leading towards implementation [28, 31]. Thus, this study is underpinned by the investigators’ earlier exploratory data resulting from qualitative [9, 26, 36, 37] and phase 1 modelling studies [15, 24, 34, 38] to define transition points where palliative care should, at minimum, be integrated. The transition points, defined by our previous work which will be used as the time of integration in this RCT, are presented in Table 1. Of note, these transition times are viewed as a minimum standard of care, with palliative care integration implemented if it has not already occurred. Consistent with the MRC framework, this phase 2 trial tests the feasibility of implementing palliative care at these transition points, before proceeding to a definitive phase 3 trial.

**Table 1 Tab1:** Transition point definitions

Prostate cancer	Presence of metastatic disease and multi-day hospital admission
Breast cancer	Presence of visceral metastatic disease (metastases involving organs other than bone only) and multi-day hospital admission
High grade glioma	Hospital presentation (inpatient or outpatient): first recurrence of primary HGG where pathological or clinical diagnosis is glioblastoma/WHO grade IV disease or first diagnosis of primary HGG and no cancer specific treatment being prescribed

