#### Randomisation

Patient-level randomisation will be centralised and coordinated by the trial coordinator who, in real time, accesses the independent blinded system, separate to the treating clinical and patient-interfacing research staff. The randomisation schedule involved 1:1 allocation and used the minimisation method to ensure a balanced distribution between groups with respect to the patient’s tumour type and hospital site. After consent and baseline data is obtained, the research nurse telephones the trial coordinator for the outcome of the randomisation process. The research nurse will liaise with the treating clinician to inform them of the outcome of randomisation.

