Satisfaction with care (carer): FAMCARE [51] is a 20-item scale developed to measure family members’ satisfaction with delivery of palliative care.

Patient-reported, cost-utility weights, measured by a cancer specific multi-attribute utility index QLU-C10D [40] is calculated based upon the recordings made by patients on the EROTC QLQ-C30 instrument.

*Feasibility and Acceptability measures:*

A. Patient/carer recruitment and retention rates:
  i. Number of identified eligible patients/carers at included hospital sites;
  ii. Number of consenting patients/carers at included hospital sites;
  iii. Number of participants reaching study completion at included hospital sites.
B. Acceptability of STEP Care intervention to patients/carers:
  i. Number of withdrawals from STEP Care intervention;
  ii. Number of adverse events arising from STEP Care intervention;
  iii. Qualitative interviews with STEP Care family carers following bereavement*.
C. Acceptability of STEP Care intervention to participating physicians:
  i. NAT: PD-C documentation completion rate by participating STEP care physicians;
  ii. Focus group with STEP Care physicians regarding perspectives on STEP care content, timing and frequency of interaction.
D. Refinement of STEP Care intervention procedures ensuring future replication:
  i. Percentage of initial STEP Care interactions occurring within planned 14 day timeframe;
  ii. Median total number of STEP Care interactions per patient/carer.
E. Refinement of outcome measures and data collection methods;
  i. To determine an estimate of effect size for potential patient- and carer- reported outcome measures and variance to inform power calculations for planned phase 3 trial.
  ii. Percentage of missing data on patient- and carer- reported outcome measures, i.e. acceptability of selected measures.
F. STEP Care intervention fidelity;
  i. Timing of intervention delivery: median number of days from enrolment to first STEP Care interaction, and subsequent STEP Care interactions.
  ii. Content of intervention: audit of random sample of 20% of audio-recorded consultations and associated documentation using the NAT: PD-C. [39]

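### The protocol says this trial's observed quality-of-life effect will give a robust phase 3 sample size, but 27 to 45 completers per arm fix that effect only to within about 0.36 to 0.55 SD

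*Protocol article*

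**What the plan says.** Four places in the protocol article link this trial's effect estimate to the size of phase 3.

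- Discussion: with quality of life as the key secondary outcome, "the effect size will enable robust calculation of the sample size".
- Secondary aims: "The key secondary outcome of effect upon quality of life will enable the appropriate sample size calculation".
- Background, last paragraph: the data will be used to "calculate effect sizes to inform a phase 3 trial".
- Appendix, feasibility and acceptability measures, item E.i: "To determine an estimate of effect size for potential patient- and carer- reported outcome measures and variance to inform power calculations".

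The first two are the firm statements: they say the effect will enable the calculation. The other two say only that it will inform it, and item E.i names the variance as well.

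The numbers available come from the Primary aim, "enrolment of 90 patients across three sites in 24 months, with at least 60% of patients progressing to study completion", with completion "defined as 12 weeks post baseline". The comparison is "STEP Care plus standard best practice cancer care versus standard best practice cancer care alone", and "The randomisation schedule involved 1:1 allocation and used the minimisation method". Planned analyses sets the sample size from what the sites can recruit. It states no precision or power target, and it plans baseline-adjusted ANCOVA reported with 95% confidence intervals.

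**The concern.** A trial sized for feasibility usually estimates a modest treatment effect poorly, while it estimates variance, retention and accrual usefully well. The firm statements claim the opposite strength: they present the effect estimate as a sound basis for sizing the next trial.

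If that claim is acted on, a chance-high estimate gives a phase 3 trial that is too small, in patients with a short prognosis. A chance-low estimate gives one several times larger than needed, and an estimate of zero or below gives no sample size at all. The question is whether the likely precision is good enough for the word *robust*.

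**Working it through.** **The plan's own figure.** Planned analyses gives 30 per treatment group and 90 in total, at about two per month per site over 24 months. With two arms, 2 × 30 = 60. The stated rate gives 2 × 3 sites × 24 = 144. Only 3 × 30 gives 90. The figures do not agree, which is a separate matter. I use 90, the number in the Primary aim.

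**Completers per arm.** At the 60% minimum: 90 × 0.60 / 2 = 27. With no loss: 90 / 2 = 45.

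**Precision.** In SD units, SE = √(2/n) × √(1 − ρ²). Here n is completers per arm and ρ is the correlation between baseline and 12-week scores. The document gives no ρ, so it is an assumption. The half-width is the t quantile (about 2.01 for 27 per arm, 1.99 for 45) times the SE.

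| Completers per arm | ρ | SE (SD) | 95% half-width (SD) |
|---|---|---|---|
| 27 | 0 | 0.272 | 0.55 |
| 27 | 0.5 | 0.236 | 0.47 |
| 45 | 0 | 0.211 | 0.42 |
| 45 | 0.5 | 0.183 | 0.36 |
| 45 | 0.7 | 0.151 | 0.30 |

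**What this does to a phase 3 size.** Assume a true effect of 0.3 SD and a phase 3 trial with two-sided 5% significance and 80% power. Without baseline adjustment it needs 2 × (1.96 + 0.84)² / 0.3² ≈ 175 per arm. Adjustment with ρ = 0.5 multiplies this by 0.75, giving about 131.

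The chance that this trial's estimate is zero or negative is Φ(−0.3/SE). If phase 3 is sized from a positive estimate e, its true power falls below 50% when e exceeds the true effect by a factor of (1.96 + 0.84)/1.96 = 1.43, that is, when e is above 0.429 SD. The factor does not depend on ρ if phase 3 uses the same adjustment. The share of such trials is P(e > 0.429) / P(e > 0), with e normal around 0.3.

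| Completers per arm | ρ | Estimate ≤ 0 | Phase 3 true power below 50%, given a positive estimate |
|---|---|---|---|
| 27 | 0 | 13.5% | 37% |
| 27 | 0.5 | 10% | 33% |
| 45 | 0 | 8% | 29% |
| 45 | 0.5 | 5% | 25% |
| 45 | 0.7 | 2% | 20% |

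The first row, worked out: 0.3/0.272 = 1.10, so Φ(−1.10) = 0.135. Then 0.129/0.272 = 0.473, so P(e > 0.429) = 0.318, and 0.318/0.865 = 0.37.

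In that row, 95% of estimates lie between 0.3 ± 1.96 × 0.272, or −0.23 to 0.83 SD. The middle half of the phase 3 sizes from positive estimates runs from about 60 to 405 per arm, against 175 needed. Also at 27 per arm without adjustment, the share below 50% power is 49% for a true effect of 0.2 SD and 22% for 0.5 SD.

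**Comparison with the SD.** With 52 degrees of freedom the 95% limits for the SD are about 0.84 to 1.24 times the estimate. Required n scales with the square of the SD, so this moves the phase 3 size by a factor of about 0.71 to 1.54. By contrast, the confidence limits around an observed effect of 0.3 SD at 27 per arm imply 23 per arm at the upper limit and no defined size at the lower.

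**The case against.** The primary aim is feasibility, efficacy is labelled preliminary throughout, and no analysis or conclusion of this trial depends on the sentence at issue. Confidence intervals are planned, so the imprecision will be visible. Variance, retention and accrual are already planned outputs. The figure of 27 per arm is the minimum for success, not the expected number, and ANCOVA improves on the unadjusted figures. Nowhere does the article say that the point estimate will be put mechanically into an 80% power formula.

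Most of this stands and limits the point. It is why the size is given as a range up to full retention and with adjustment, and why the sizing rule is stated as an assumption. It does not rescue the claim: even full retention with ρ = 0.7 leaves a half-width as large as a 0.3 SD effect. Full retention is also unlikely, since the Background describes the transition points as heralding a prognosis of under six months. If 30 per group were the real target, 60% completion would leave 18 per arm, and precision would be worse.

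A reader might infer two stronger points, and the documents support neither.

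- **Upward bias from selection.** QUAL-E and QLQ-C30 have several scales, measured at several visits, so one might suppose the largest effect will be carried forward. The article does not say so, and the full protocol or analysis plan may fix the scale and visit.
- **A disappointing estimate would wrongly end the programme.** The only stated criterion is feasibility. No stop or go rule rests on quality of life.

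**Conclusion.** The point holds as an overclaim in the text. The Secondary aims and Discussion attribute to the quality-of-life effect estimate a reliability that 90 patients with at least 60% completion cannot give. The 95% half-width is about 0.36 to 0.55 SD for 27 to 45 completers per arm and ρ of 0 to 0.5. It falls to about 0.30 SD only with full retention and ρ = 0.7.

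For a true effect of 0.3 SD, sizing phase 3 from a positive estimate would leave about 25% to 37% of such trials with true power below 50%, and about 5% to 13.5% of estimates would give no size at all. These figures rest on the assumed true effect, the assumed ρ, two-sided 5% significance, 80% power, and use of the point estimate as the design effect. The direction does not depend on the exact values. The absence of a minimal important difference from a condensed article is not itself the fault; the stated robustness is.

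**What to change.** Reword the four places listed above (Background, Secondary aims, Discussion, and Appendix item E.i) to say that:

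- phase 3 will be powered on a prespecified minimal important difference for the chosen quality-of-life scale;
- this trial will supply the SD (with allowance for its uncertainty, for example an upper confidence limit), the baseline correlation, 12-week retention and accrual;
- the observed effect will be reported with its 95% confidence interval and will not serve as the design effect.

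Drop *robust* from the Discussion sentence. Nothing changes in conduct, sample size or data collection. The cost is a more modest statement of what this trial delivers.

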## Appendix

### Study measures

Quality of life at the end of life (patient): (QUAL-E [44]). The QUAL-E is a measure of quality of life specifically targeting those with advanced illness, examining four domains: life completion, impact of symptoms, relationships with health care providers and preparation for end of life. It has demonstrated acceptable validity and reliability, is acceptable to patients and shows consistent performance across different demographic and disease groups.

Health-related quality of life and symptom impact (patient): EORTC QLQ-C30 [41, 42]. The EORTC QLQ-C30 is a widely used instrument to measure quality of life in cancer patients. Consisting of 30 items, this includes 5 functional scales (physical, role, emotional, cognitive and social), 3 symptom scales (fatigue, nausea and vomiting and pain), 6 single items of symptoms/other and a global health status/QOL scale. Designed for self-completion, it has been extensively validated for this population [45].

Quality of life (carer): CQOL-C [46]. Caregiver Quality of Life-Cancer is a 35-item instrument which has been developed specifically for family caregivers of people with cancer. Designed for self-completion, it has been shown to have adequate validity, test-retest reliability and internal consistency in this target population.

Mood (patient and carer): Depression, Anxiety, Stress Scale (DASS-21 [47]). The DASS-21 is a short-form of the DASS instrument and consists of three self-report scales measuring the states of depression, anxiety and stress. The scales have high internal consistency and yield meaningful discriminations in a variety of settings, and acceptable construct validity.

Performance status (patient): AKPS [48]. Australian-modified Karnofsky Performance Status (between 10 and 100) is a single score which measures the patient’s overall performance status or capacity to perform usual activities of daily living.

Illness understanding (patient and carer): [49] Developed by Temel and colleagues to assess the patient’s level of information and understanding of the goals of cancer treatment, patients are asked to nominate if their cancer is curable (or not) and the intention of the cancer treatment.

Preparedness to care (carer): PCS [50]. This 8-point scale provides a measure of the degree to which carers feel able and equipped to take on caring roles.

Satisfaction with care (carer): FAMCARE [51] is a 20-item scale developed to measure family members’ satisfaction with delivery of palliative care.

Patient-reported, cost-utility weights, measured by a cancer specific multi-attribute utility index QLU-C10D [40] is calculated based upon the recordings made by patients on the EROTC QLQ-C30 instrument.

*Feasibility and Acceptability measures:*

A. Patient/carer recruitment and retention rates:
  i. Number of identified eligible patients/carers at included hospital sites;
  ii. Number of consenting patients/carers at included hospital sites;
  iii. Number of participants reaching study completion at included hospital sites.
B. Acceptability of STEP Care intervention to patients/carers:
  i. Number of withdrawals from STEP Care intervention;
  ii. Number of adverse events arising from STEP Care intervention;
  iii. Qualitative interviews with STEP Care family carers following bereavement*.
C. Acceptability of STEP Care intervention to participating physicians:
  i. NAT: PD-C documentation completion rate by participating STEP care physicians;
  ii. Focus group with STEP Care physicians regarding perspectives on STEP care content, timing and frequency of interaction.
D. Refinement of STEP Care intervention procedures ensuring future replication:
  i. Percentage of initial STEP Care interactions occurring within planned 14 day timeframe;
  ii. Median total number of STEP Care interactions per patient/carer.
E. Refinement of outcome measures and data collection methods;
  i. To determine an estimate of effect size for potential patient- and carer- reported outcome measures and variance to inform power calculations for planned phase 3 trial.
  ii. Percentage of missing data on patient- and carer- reported outcome measures, i.e. acceptability of selected measures.
F. STEP Care intervention fidelity;
  i. Timing of intervention delivery: median number of days from enrolment to first STEP Care interaction, and subsequent STEP Care interactions.
  ii. Content of intervention: audit of random sample of 20% of audio-recorded consultations and associated documentation using the NAT: PD-C. [39]
